### Genotyping

Buccal cell samples are collected by FLOQSwab hDNA Free buccal brushes (Copan Brescia, Italy). Genomic DNA extraction is performed with a Quick DNA Miniprep plus Kit (ZymoResearch, California, USA) according to the manufacturer’s instructions.

In our trial, we investigate the genetic variants reported in the PharmGKB database (www.pharmgkb.org) with a clinical annotation of evidence of association with AD response classified as levels 1a, 1b, 2a, and 2b.

Our PGx test includes 31 genetic variants. Thirty single-nucleotide polymorphisms (SNPs) are genotyped with customized TaqMan OpenArray plates on a QuantStudio 12K Flex Real-Time PCR System (Applied Biosystems, Foster City, California, USA) according to the manufacturer’s instructions (15 in *CYP2D6*, 10 in *CYP2C19*, and four in *MC4R*, *FKBP5*, *HTR1A*, and *HTR2A*). The data are analyzed with the Genotyping application on Thermo Fisher Cloud. Moreover, copy number variation (CNV) of the *CYP2D6* gene is evaluated using the TaqMan Copy Number Assay mix specific for *CYP2D6* exon 9 (Assay ID: Hs00010001_cn) according to the manufacturer’s instructions and with a C_T_ threshold of 0.2, and the analysis is performed with CopyCaller Software (Applied Biosystems). Using AlleleTyper Software (Life Technologies, California, USA), we integrate the SNP genotyping results with the copy number information for the *CYP2D6* gene to obtain all the eventual *CYP2D6* and *CYP2C19* diplotypes. Diplotypes with higher allele frequencies in the European population are selected if it cannot be determined with certainty. The translation is based on the translation table obtained from the PharmGKB database.

Participants are also genotyped for the 5-HTTLPR (short/long allele) in the SLC6A4 gene by PCR amplification of the relevant genomic location using the KAPA HiFi HotStart PCR Kit (Roche Diagnostics, Basel, Switzerland) and the following primers: 5′–ATGCCAGCACCTAACCCCTAATGT–3′ (forward) and 5′–GGACCGCAAGGTGGGCGGGA–3′ (reverse). The genotype is then determined by electrophoresis and visualization of the amplified products on a 2% agarose gel.

### Pharmacogenomic (PGx) test report

Considering the resulting genetic profile, a personalized PGx report is generated. The diplotypes obtained for the *CYP2D6* and *CYP2C19* genes are associated with the matching metabolizer phenotypes: ultra-rapid, normal, intermediate, and poor for *CYP2D6*, and ultra-rapid, rapid, intermediate, poor, normal, likely intermediate, and likely poor for *CYP2C19.*

According to both the Clinical Pharmacogenetics Implementation Consortium (CPIC) and the Dutch Pharmacogenetics Working Group (DPWG) guidelines, the report places the most ADs widely used in Italy into three recommended categories: (1) “use as directed” (labeled “green”), (2) “use with caution” (labeled “yellow”), and (3) “use with extreme caution” (labeled “red”) (see Fig. 3 for an example of a report for one patient). In addition, drug details associated with each medication in the yellow or red categories are provided. The current AD is excluded from the report to avoid clinician bias in decision-making. The clinicians have access to the PGx report through an interactive web interface.

**Fig. 3 Fig3:**
[figure not shown]
Example of a report. The report shows the classification of drugs in the three recommended categories, green (“use as directed”), yellow (“use with caution”), and red (“use with extreme caution”). The current AD (“1st drug”) is excluded from the list to avoid clinician bias in decision-making

Before study initiation, training was provided to all participating investigators on the interpretation of genetic testing results and on the relevance of each genetic variant to pharmacotherapy.

### Pharmacokinetic analysis

Pharmacokinetic evaluation is conducted at weeks 4, 8, and 12 in the TAU group and the non-responder patients in the TGTG group. Serum concentrations of the ADs and their metabolites are measured at a steady-state on the same day of clinical evaluation. Blood samples for pharmacokinetic analysis are drawn at 8 a.m. before the morning AD dose. Determination of the serum concentrations of the ADs and their metabolites are performed by using high-performance liquid chromatography procedures.

### Further pharmacogenomics analysis

To better elucidate the molecular mechanisms underlying the response to the ADs, for all non-responder patients in our trial, further PGx analysis will be carried out. In particular, we will first investigate, always through a TaqMan OpenArray approach, further genetic variants known to be involved in the response to ADs or their side effects that are already described in literature studies and in the PharmGKB database. Moreover, for those patients (belonging to both the TGTG and TAU groups) who do not benefit from the assigned treatment, sequencing of all the genes associated with both AD response and susceptibility to side effects will be conducted with the aim of identifying novel rare functional variants.

### Sample size

Based on previous PGx studies performed on MDD patient cohorts [19, 20], the sample size needed to detect a significant reduction in symptom scores was calculated. The analysis revealed that a sample size of 225 participants (⁓112 per group) is required to observe a 15% reduction in symptom scores with a common standard deviation of 45%, alpha = 0.05, and power = 80%. Assuming an estimated drop-out rate of 20–25%, as already observed in follow-up studies on MDD [21], a total sample size of 300 participants will be enrolled in this study.

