### Statistical analysis

Analysis of variance (ANOVA) or the Kruskal–Wallis and Mann–Whitney *U* nonparametric tests and the chi-squared test will be used to analyze differences in continuous and categorical variables, respectively, between groups. Pearson’s correlation analysis will be used to evaluate bivariate correlations. Parametric and nonparametric tests will be used to meet relative assumptions (i.e., distribution, sample size).

To pursue our primary outcome, the analyses will be performed for patients who complete the study through week 8. The analysis will be performed using mixed-effects models with repeated measures (MMRM) to examine the effect of time and group (TGTG vs. TAU) on the reduction in the HAMD-17 score. The model includes the fixed effect continuous factor baseline HAMD-17 and fixed effect categorical factors, which are the treatment group (TGTG and TAU; 2 levels), visit (weeks 4 and 8; 2 levels), and treatment x visit interaction. The mean changes in the HAMD-17 at week 8 in the TGTG and TAU groups will be estimated and tested utilizing the LS means from the treatment x visit interaction in the MMRM model. The primary analysis will test the difference (contrast) between the week 8 least squares (LS) means at a two-sided significance of 0.05. To achieve the secondary outcome, the generalized linear mixed model will be used for response and remission analyses. The analyses of the tertiary outcomes will be performed for exploratory purposes with the same statistical models. Comparisons between the TGTG and TAU means at all timepoints of evaluation will also be performed for descriptive purposes. Finally, an intention-to-treat (ITT) analysis will be performed for all the patients who undergo at least one post-treatment assessment for efficacy during the study. The last observation will be carried forward on the HAMD-17. All the statistical analyses will be performed using R Statistical Software (R Foundation for Statistical Computing, Vienna, Austria).

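### The 225 evaluable participants match a one-sided 5% calculation; for the two-sided primary test they give about 70–73% power before covariate adjustment, not 80%

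*Protocol article*

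**What the plan says.** The primary outcome (Outcomes section) is percent change in HAMD-17 from baseline to week 8, compared between the two groups.

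The Sample size section states that 225 participants, roughly 112 per group, "is required to observe a 15% reduction in symptom scores with a common standard deviation of 45%, alpha = 0.05, and power = 80"%. It allows for 20–25% drop-out and concludes that "a total sample size of 300 participants will be enrolled in this study". It gives no sidedness for alpha, no named test, and no allowance for covariates or repeated measures.

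The Statistical analysis section restricts the primary analysis to patients who complete through week 8. It fits an MMRM with baseline HAMD-17, treatment, visit (weeks 4 and 8) and treatment by visit, and then states: "The primary analysis will test the difference (contrast) between the week 8 least squares (LS) means at a two-sided significance of 0.05".

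**The concern.** The Sample size section gives every input needed to check its result, and the result does not fit the declared two-sided test. The difference, SD, alpha and power imply a clearly larger number than 225.

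The stake is how the trial will be read. A non-significant result would be taken as coming from a design with a 20% chance of missing the planned effect. On the plan's own inputs, before covariate adjustment, that chance is 27–30%. The treatment estimate is not biased, and the type I error rate of the two-sided test is not affected.

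**Working it through.** **Inputs** (Sample size section unless noted)
- Difference between groups: 15 percentage points. The stated 15% is read on the scale of the primary outcome, percent change in HAMD-17.
- Common SD: 45 percentage points, so d = 15/45 = 0.333.
- Alpha 0.05, power 80%; two equal groups (about 112 each).
- Sidedness: not given there; two-sided in Statistical analysis.
- Drop-out 20–25%; 300 enrolled.

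**Formula for two independent means, normal approximation**

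n per group = 2 × (z_alpha + z_beta)² × (SD/difference)² = 2 × (z_alpha + z_beta)² × 9

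**Step 1. Reproduce the plan's figure**
- One-sided 0.05: 2 × (1.645 + 0.842)² × 9 = 111.3 per group. With the t distribution it is 111.97, so 112 per group and 224 in total. This matches the stated 225 and about 112 per group.
- Drop-out: 225/0.75 = 300. This matches the enrolment target, so the inflation step is correct.

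**Step 2. Use the declared two-sided test**
- Two-sided 0.05: 2 × (1.960 + 0.842)² × 9 = 141.3, so 142 per group and 284 in total. With the t distribution it is 142.2, so 143 per group and 286 in total.
- Against 225 this is a shortfall of about 60 evaluable patients (284/225 = 1.26).

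**Step 3. Two-sided power at the planned size**

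Power ≈ Φ(0.333 × √(n/2) − 1.960), with n per group.

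| Evaluable | Drop-out from 300 | n per group | Normal approx. | t-test |
|---|---|---|---|---|
| 225 | 25% | 112.5 | Φ(2.500 − 1.960) = 70.5% | 70.2% |
| 240 | 20% | 120 | Φ(2.582 − 1.960) = 73.3% | 73.0% |
| 300 | none | 150 | 82.3% | 82.1% |

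The chance of missing a true 15-point difference is therefore about 30% at 225 and 27% at 240. To have 284 evaluable out of 300, losses could not exceed 16/300 = 5.3%.

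**Step 4. Difference detectable with 80% two-sided power**

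Difference = (1.960 + 0.842) × 45 × √(2/n)
- 225 evaluable: 16.8 points (16.9 with the t distribution).
- 240 evaluable: 16.3 points by either method.

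**Step 5. What covariate adjustment would have to deliver**

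If the covariate–outcome correlation is r, the residual SD is 45 × √(1 − r²). To restore 80% power at a 15-point difference, 1 − r² must equal (15/detectable difference)².
- 225 evaluable: (15/16.88)² = 0.789, so r² = 0.21 and r ≈ 0.46.
- 240 evaluable: (15/16.34)² = 0.843, so r² = 0.16 and r ≈ 0.40.

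The document gives no value for r. Taking r from 0.3 to 0.5 purely as an assumption, power at 225 evaluable runs from 74.6% to 82.3% (normal approximation).

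**Step 6. Could another method explain 225?**

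A rank test would raise the two-sided requirement to about 142/0.955 = 149 per group, which is further from 112. The t distribution also raises it. Among the unadjusted two-group calculations tried, only the one-sided one gives the stated figure.

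**The case against.** **The cause is not documented.** The Sample size section says only "alpha = 0.05, and power = 80"%, and its inputs come from cited studies that are not at hand. A reader might infer that a one-sided test was deliberately used for planning. The text does not say so; the one-sided origin is an inference from an exact numerical match. This objection stands as to the cause. It does not remove the mismatch, because 225 is not the two-sided answer to the stated inputs wherever it came from.

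**The primary analysis is not an unadjusted t-test.** It is an MMRM with baseline HAMD-17 as a covariate, so actual power may exceed 70–73%. This stands too. A reader might conclude that the trial simply has 70% power, but that figure is the unadjusted one at the worse end of the drop-out range. Equally, 80% cannot be credited to the model, because the sample-size paragraph states no correlation or variance reduction.

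**300 are enrolled, and 300 would give about 82%.** This requires no loss at all. The plan itself expects to lose 20–25% and analyses week 8 completers. A reader might also infer that analysing everyone randomised, or adjusting for a covariate, would win the power back. Neither follows: including patients who drop out does not restore the information in their missing week 8 scores, and baseline HAMD-17 is already in the primary model.

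**Severity.** Nothing here affects bias or type I error, and recruitment has been under way since February 2020. That limits the consequence to a wrong power statement, but power for the primary outcome is a headline design property.

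**Conclusion.** The power statement is wrong as written for the primary test that the plan declares. On the stated 15-point difference and SD of 45, the two-sided 0.05 contrast needs 284–286 evaluable patients; the plan provides for 225–240. Two-sided power before covariate adjustment is about 70–73%, and the difference detectable with 80% power is about 16.3–16.9 points.

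This rests on three readings: the 15% is a between-group difference in percentage points, allocation is equal, and drop-out falls in the plan's own 20–25% range. The first two are supported by the fact that they reproduce the stated 225. The size of any gain from baseline adjustment cannot be settled from the document.

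**What to change.** Keep the two-sided test. Moving to a one-sided test to fit the number would weaken the error control already declared.

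Revise the sample-size paragraph so that it:
1. states the sidedness of alpha and the test behind the calculation;
2. says that with 225–240 evaluable patients, a 15-point difference and an SD of 45, two-sided power at 0.05 is about 70–73% for an unadjusted comparison;
3. gives the difference detectable with 80% power as about 16.9 points (225 evaluable) to 16.3 points (240 evaluable);
4. if 80% is still claimed through the baseline-adjusted MMRM, states the assumed covariate–outcome correlation (about 0.46 needed at 225, about 0.40 at 240) and its source.

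The cost is wording and a less favourable power figure. No extra patients and no change of analysis are needed to correct the statement. For scale, 80% unadjusted power on the stated inputs would mean enrolling 284/0.80 = 355 to 284/0.75 = 379 patients.

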### Data management

The data management process is the responsibility of the project coordinator. Both clinical and biological data collection, analysis, storage, security, and sharing are consistent with the standard operating procedures that ensure patient pseudonymization.

### Baseline demographic and clinical features

Age (years) and mean (SD); gender (%F); education (years) and mean (SD); race (%); smokers (%); body mass index (BMI) and mean (SD); age of onset (years) and mean (SD); depression category; moderate, severe, or very severe (%); recurrence (%); presence of psychotic symptoms (%); comorbidity with personality disorders congruent with inclusion/exclusion criteria (%); comorbidity with anxiety disorders (%); presence of psychiatric disorders among the first-degree relatives (%); HAMD-17 at baseline and mean (SD); BDI-II at baseline and mean (SD); BAI-II at baseline and mean (SD); mini-ICF-APP at baseline and mean (SD); MMSE at baseline and mean (SD); UKU at baseline and mean (SD); previous failed adequate treatment; CECA-Q mother antipathy (hostility, coldness) (%); CECA-Q father antipathy (hostility, coldness) (%); CECA-Q mother neglect (%); CECA-Q father neglect (%); CECA-Q physical abuse mother (%); CECA-Q physical abuse father (%); CECA-Q sexual abuse (%); and Paykel score and means (SD).

### Statistical analysis

Analysis of variance (ANOVA) or the Kruskal–Wallis and Mann–Whitney *U* nonparametric tests and the chi-squared test will be used to analyze differences in continuous and categorical variables, respectively, between groups. Pearson’s correlation analysis will be used to evaluate bivariate correlations. Parametric and nonparametric tests will be used to meet relative assumptions (i.e., distribution, sample size).

To pursue our primary outcome, the analyses will be performed for patients who complete the study through week 8. The analysis will be performed using mixed-effects models with repeated measures (MMRM) to examine the effect of time and group (TGTG vs. TAU) on the reduction in the HAMD-17 score. The model includes the fixed effect continuous factor baseline HAMD-17 and fixed effect categorical factors, which are the treatment group (TGTG and TAU; 2 levels), visit (weeks 4 and 8; 2 levels), and treatment x visit interaction. The mean changes in the HAMD-17 at week 8 in the TGTG and TAU groups will be estimated and tested utilizing the LS means from the treatment x visit interaction in the MMRM model. The primary analysis will test the difference (contrast) between the week 8 least squares (LS) means at a two-sided significance of 0.05. To achieve the secondary outcome, the generalized linear mixed model will be used for response and remission analyses. The analyses of the tertiary outcomes will be performed for exploratory purposes with the same statistical models. Comparisons between the TGTG and TAU means at all timepoints of evaluation will also be performed for descriptive purposes. Finally, an intention-to-treat (ITT) analysis will be performed for all the patients who undergo at least one post-treatment assessment for efficacy during the study. The last observation will be carried forward on the HAMD-17. All the statistical analyses will be performed using R Statistical Software (R Foundation for Statistical Computing, Vienna, Austria).

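### The primary MMRM is restricted to week-8 completers, a post-randomisation selection that drops the week-4 scores of patients who leave

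*Protocol article*

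**What the plan says.** All of the following is in the protocol article.

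- **Statistical analysis, primary population:** "To pursue our primary outcome, the analyses will be performed for patients who complete the study through week 8".
- **Statistical analysis, model:** "The analysis will be performed using mixed-effects models with repeated measures (MMRM"), with baseline HAMD-17, treatment group, "visit (weeks 4 and 8; 2 levels), and treatment x visit interaction". The test is of the "difference (contrast) between the week 8 least squares (LS) means at a two-sided significance of 0.05".
- **Statistical analysis, broader set:** at the end of the section, "an intention-to-treat (ITT) analysis will be performed for all the patients who undergo at least one post-treatment assessment for efficacy", with the last HAMD-17 observation carried forward. This analysis is not labelled primary.
- **Sample size:** "Assuming an estimated drop-out rate of" 20–25%, which takes 225 evaluable patients to 300 enrolled.
- **Pharmacogenetic report and intervention procedure:** patients who change to another monotherapy stay in the study. Those who need combination or augmentation are excluded from it.
- **Blinding:** the treating physicians know the allocation.
- **Aim of the study:** the test is meant to improve response and to reduce side effects.

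**The concern.** Randomisation makes the two arms comparable at baseline. It does not make the week-8 completers of the two arms comparable, because completion is itself a possible consequence of allocation. Three features make that more than a formality here. Patients whose depression calls for augmentation or combination are taken out, the prescriber who judges that need is unblinded, and poor response and side effects are both plausible reasons to leave as well as the things the test is meant to change.

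The restriction also works against the model. A likelihood-based MMRM is valid under missing at random (MAR) because a patient with a week-4 score and no week-8 score still contributes. Once only completers enter, no such patient is left, and the week-8 contrast is close to an ANCOVA on completers.

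At stake is the trial's single confirmatory test: its estimate may be biased by an amount that the completers' data alone cannot reveal.

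**Working it through.** **Step 1. How many patients the rule could remove.** From the Sample size section: 300 enrolled, drop-out 20–25%.

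- 300 × 0.20 = 60 and 300 × 0.25 = 75 removed, leaving 240 or 225.
- The plan's own inflation reproduces at the upper rate: 225 / (1 − 0.25) = 300.
- If the 20–25% covers all 12 weeks, the loss by week 8 is smaller.

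**Step 2. Size and direction of the bias (illustrative).**

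From the document: SD 45, difference of interest 15 points, 300 patients (150 per arm).

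Assumed, because the document does not give them:
- correlation of 0.6 between week 4 and week 8;
- mean improvement of 30% at week 4 and 40% at week 8 in TAU, with 60% of the true effect present by week 4;
- drop-out after week 4 through a logistic model in which poorer week-4 response raises the chance of leaving, with a log-odds slope of 1 to 1.5 per SD in both arms;
- no baseline adjustment.

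The completer estimate is shifted by

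shift = ρ × SD × (m_TGTG − m_TAU) = 0.6 × 45 × (m_TGTG − m_TAU) = 27 × (m_TGTG − m_TAU),

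where m is the mean among completers of the week-4 deviation from the arm's own mean, in SD units. The arm that loses more poor responders has the larger m.

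| Loss TAU / TGTG | True difference | Completer estimate | LOCF estimate |
|---|---|---|---|
| 30% / 15% | 0 | −3.3 to −4.1 | +2.7 to +2.9 |
| 30% / 15% | 15 | 11.8 to 10.9 | 16.8 to 17.0 |
| 25% / 20% | 0 | −1.1 to −1.4 | +0.9 to +1.0 |
| 25% / 20% | 15 | 13.9 to 13.6 | 14.7 to 14.8 |
| equal (22.5%), same mechanism | 0 | 0 | 0 |

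In each range the first figure is for slope 1 and the second for slope 1.5. For example, at 30% / 15% with slope 1, m_TGTG − m_TAU is about −0.12, and 27 × (−0.12) is about −3.2 (−3.25 before rounding). Simulations of 4,000 trials with the same basic set-up agree: at 29% / 15% with slope 1 the completer estimates were −3.1 and 11.3 for true differences of 0 and 15, and an estimate using all available week-4 and week-8 data gave 0.1 and 15.0.

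The sign follows the arm with the greater loss. Here TAU loses more poor responders, so the TAU completers look too good and the shift runs against the test. With the losses reversed and no true effect, the same shift would favour it.

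Similar overall rates are not sufficient protection. With 22% loss in TGTG and 24% in TAU, but loss related to outcome in TAU only, the simulated completer estimate under a true zero was −6.1.

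**Step 3. Precision.** Power for 15 points, SD 45, two-sided 0.05 is Φ(15 / (45 × √(2/n)) − 1.96), with n per arm.

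- Completers: n = 112.5 gives Φ(2.50 − 1.96) = 0.71 (0.70 with 112 per arm and the t distribution). n = 120 gives Φ(2.58 − 1.96) = 0.73.
- All available data, if every drop-out has a week-4 score: effective n = 150 / (ρ² + (1 − ρ²)/p), where p is the fraction with week 8.
  - p = 0.75: 150 / (0.36 + 0.64/0.75) = 150 / 1.213 = 123.6, power Φ(2.62 − 1.96) = 0.75.
  - p = 0.80: 150 / (0.36 + 0.64/0.80) = 150 / 1.16 = 129.3, power Φ(2.68 − 1.96) = 0.76.

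The gain is therefore about 3 to 4 percentage points at most, and less if some drop-outs have no week-4 score.

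**The case against.** **The bias figures rest on a drop-out pattern that the document does not give.** This stands. The Sample size section gives one pooled rate with no split by arm, no reasons and no time window. The all-available estimate looks unbiased in these scenarios because drop-out was generated as MAR given week 4, so they do not show how it would behave if MAR failed. The figures illustrate and do not predict.

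**Some poor responders are retained.** This also stands: a further change of monotherapy does not end participation. The exclusion for combination or augmentation remains, however, and it is likely to select on outcome.

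**A broader analysis is already planned.** A reader might infer that the trial has no analysis beyond completers. The document does not support that, since an ITT set is defined. But it comes last, is not primary and relies on LOCF, which in the unequal-loss scenarios under a true zero errs in the opposite direction from the completers analysis. The two planned analyses could disagree with both of them biased.

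**Stronger readings that do not hold.**
- A reader might infer that the completer rule would manufacture a benefit. In the scenarios tabulated it dilutes one, and the document does not settle the direction.
- A reader might infer that the rule costs the gap between 70–73% power and the 82% available if all 150 per arm had week-8 data. No analysis can recover unobserved week-8 scores in full. The low starting power belongs to a separate matter: 225 reproduces only with a one-sided 0.05, whereas the test is two-sided.
- A reader might infer that "visit (weeks 4 and 8; 2 levels") is an error because week 12 is left out. Two visits suffice for a week-8 endpoint.
- The protocol does not say why MMRM was chosen, so no motive should be attributed.

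**Conclusion.** The concern holds. The restriction is stated outright, so it is not a detail left to an unseen analysis plan. It conditions the only confirmatory test on a post-randomisation event that can depend on outcome and arm, and it discards week-4 data that the chosen model could use.

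The size cannot be fixed from the document. Under the assumptions listed, the shift is about 3 to 4 points of a 15-point effect with 30% against 15% loss, about 1 to 1.5 points with 25% against 20%, and near zero with equal loss by the same mechanism. The precision argument is secondary: about 70–73% power becomes at most about 75–76%. The case for change therefore rests mainly on the principle of the primary comparison, and it should be settled before any unblinded analysis.

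**What to change.** Replace the sentence that defines the primary population. The primary analysis becomes the MMRM on all randomised patients with a baseline and at least one post-baseline HAMD-17, analysed in the arm to which they were randomised, without LOCF, and with the week-8 contrast as the primary test. This is essentially the set that the section already calls ITT. Keep the week-8 completers analysis as a labelled sensitivity analysis. Adding week 12 as a third visit is optional.

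The cost is one sentence, with no new assessments and no change of endpoint. The primary result would then rest on MAR, which should be stated. Two limits remain. Requiring one post-baseline score is itself a post-randomisation condition, so patients with none are still not recovered. Nor does the change recover later scores for patients excluded because they needed combination or augmentation. The number of such patients in each arm, and of all losses by arm, reason and visit, should be reported beside the primary result.
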